## Abstract

**Background:**

Delirium is a common complication in elderly patients after surgery and associated with increased morbidity and mortality. Studies suggest that deep anesthesia and intense pain are important precipitating factors of postoperative delirium. Neuraxial block is frequently used in combination with general anesthesia for patients undergoing major thoracic and abdominal surgery. Compared with general anesthesia alone and postoperative intravenous analgesia, combined epidural-general anesthesia and postoperative epidural analgesia decreases the requirement of general anesthetics during surgery and provided better pain relief after surgery. However, whether combined epidural-general anesthesia plus epidural analgesia is superior to general anesthesia plus intravenous analgesia in decreasing the incidence of postoperative delirium remains unknown.

**Methods/design:**

This is a multicenter, open-label, randomized, parallel-controlled clinical trial. One thousand eight hundred elderly patients (age range 60–90 years) who are scheduled to undergo major thoracic or abdominal surgery are randomized to receive either general anesthesia plus postoperative intravenous analgesia or combined epidural-general anesthesia plus postoperative epidural analgesia. The primary outcome is the 7-day incidence of postoperative delirium. Secondary outcomes include the duration of postoperative delirium, the intensity of pain during the first three days after surgery, the 30-day incidences of postoperative non-delirium complications, the length of stay in hospital after surgery and 30-day all-cause mortality.

**Discussion:**

Results of the present study will provide information to guide clinical practice in choosing appropriate anesthesia-analgesia method for elderly patients undergoing major thoracic and abdominal surgery.

**Trial registration:**

The study is registered on ClinicalTrials.gov NCT01661907 and Chinese Clinical Trial Registry ChiCTR-TRC-12002371.

## Background

Delirium is an acute mental syndrome characterized by (1) disturbance of consciousness with reduced ability to focus, sustain and shift attention, (2) change in cognition (such as memory deficit, disorientation, or language disturbance) or development of a perceptual disturbance that is not better accounted for by a preexisting, established or evolving dementia, and (3) disturbance developing over a short period of time (usually hours to days) and tending to fluctuate during the course of the day [1].

Postoperative delirium is a common complication in the elderly after surgery. The reported incidences vary widely (from 0 % to 73.5 %) with an overall incidence of 36.8 %, and the incidence increases with age [2]. In the sickest patients in the intensive care unit (ICU), the incidence can be up to 80 % [3]. In our previous studies, delirium occurred in 51 % of patients after cardiac surgery [4] and in 44.5 % of those after non-cardiac surgery [5]. The occurrence of postoperative delirium is associated with worse outcomes, including prolonged length of stay in the ICU and hospital, increased morbidity and mortality, compromised long-term cognitive function and physical ability, and elevated medical care costs [6–15]. The most effective way to minimize such adverse outcomes is the prevention of its occurrence. At present, however, strategies that can effectively prevent the occurrence of postoperative delirium are limited [16, 17].

The causes of postoperative delirium are multifactorial and include predisposing and precipitating factors [18]. Studies found that deep anesthesia and intense postoperative pain are important precipitating factors [17, 19]. In a retrospective cohort study of patients undergoing aortic surgery, deep anesthesia (bispectral index reduction > 25 % from baseline) was associated with high incidences of postoperative delirium and neurological events [20]. In a randomized controlled trial of patients undergoing minor ophthalmic surgery, auditory evoked potential-guided anesthesia reduced the requirement of anesthetic agents and relieved early postoperative cognitive decline [21]. In two randomized controlled trials of elderly patients undergoing major noncardiac surgery, bispectral index-guided general anesthesia reduced anesthetic exposure and episodes of deep anesthesia, and decreased the incidences of postoperative delirium [22, 23].

Opioid is the mainstay of postoperative analgesia. However, high-dose opioids are associated with an increased risk of postoperative delirium [24, 25]. In a pilot randomized clinical trial, use of gabapentin as an add-on agent of postoperative analgesia reduced the occurrence of postoperative delirium, possibly due to its opioid-sparing effect [26]. In a prospective observational study of elderly patients undergoing total hip or knee arthroplasty, supplemental use of opioid-sparing drugs (gabapentin, paracetamol, and celecoxib) for postoperative analgesia was associated with a reduced incidence of delirium [27].

Neuraxial anesthesia and analgesia are used in patients undergoing lower abdominal or lower extremity surgery. When compared with general anesthesia and intravenous analgesia, neuraxial anesthesia and analgesia provides more postoperative benefits, including better pain relief, shortened length of stay in the ICU and hospital, and reduced morbidity and mortality [28–33]. Meta-analyses showed that regional anesthesia decreases the risk of postoperative cognitive dysfunction, but not delirium, when compared to general anesthesia [34, 35].

For patients undergoing major thoracic and abdominal surgery, neuraxial block can be performed in combination with general anesthesia. Studies showed that, compared with general anesthesia and postoperative intravenous analgesia, combined epidural-general anesthesia and postoperative epidural analgesia decreased the requirement of general anesthetics during surgery and provided better pain relief after surgery [36–39]. We hypothesize that combined epidural-general anesthesia and epidural analgesia may be superior to general anesthesia and intravenous analgesia in decreasing the incidence of postoperative delirium. So far, this effect has not been evaluated in previous studies [40–42].

The purpose of this study is to investigate whether two different anesthesia-analgesia methods (combined epidural-general anesthesia plus postoperative epidural analgesia versus general anesthesia plus postoperative intravenous analgesia) would lead to a difference in the incidence of postoperative delirium in elderly patients after major thoracic and abdominal surgery.

## Methods/design

### Study design

This is a multicenter, open-label, randomized controlled clinical trial with two parallel arms, combined epidural-general anesthesia plus postoperative epidural analgesia group (EGA group) and general anesthesia plus postoperative intravenous analgesia group (GA group). A total of 1800 patients undergoing major thoracic and abdominal surgery will be recruited, with 900 patients for each group. The study is coordinated by the Department of Anesthesiology and Critical Care Medicine of Peking University First Hospital, and Peking University Clinical Research Institute is responsible for the study monitoring, data management and data analysis. Other centers participating in the study include Peking University People’s Hospital, Peking University Third Hospital, Beijing Hospital, and Beijing Shijitan Hospital, all of which are teaching hospitals of Peking University.

### Ethics approval

The study protocol has been approved by the Peking University Institutional Review Board (IRB) (IRB00001052-11048). Any protocol modifications will be submitted for the IRB review and approval. The study has been registered at ClinicalTrials.gov (NCT01661907) and Chinese Clinical Trial Registry (ChiCTR-TRC-12002371). Written informed consent will be obtained from each patient or, if the patient cannot provide informed consent, from the surrogate of the patient.

### Participants

The inclusion criteria are (1) elderly patients (age range 60–90 years), (2) scheduled to undergo open thoracic or open abdominal surgery with an expected duration of 2 hours or longer. For those who undergo thoracoscopic or laparoscopic surgery, the expected length of incision must be 5 centimeters or more, and (3) agree to receive patient-controlled postoperative analgesia.

Patients who meet any of the following criteria will be excluded: (1) previous history of schizophrenia, epilepsy or Parkinson disease, or unable to complete preoperative assessment due to severe dementia, language barrier or end-stage disease; (2) history of myocardial infarction within 3 months before surgery; (3) any contraindication to epidural anesthesia and analgesia, including abnormal vertebral anatomy, previous spinal trauma or surgery, severe chronic back pain, coagulation disorder (prothrombin time or activated partial prothrombin time longer than 1.5 times of the upper limit of normal, or platelet count of less than 80 × 10^9^/L), local infection near the site of puncture, and severe sepsis; (4) severe heart dysfunction (New York Heart Association functional classification 3 or above), hepatic insufficiency (Child-Pugh grades C), or renal insufficiency (serum creatinine of 442 μmol/L or above, with or without serum potassium of 6.5 mmol/L or above, or requirement of renal replacement therapy); or (5) any other conditions that were considered unsuitable for study participation.

### Personnel training and delirium assessment

Prior to the study, study personnel are trained to follow the study protocol according to the Good Clinical Practice principles. They are also trained by a psychiatrist to assess delirium with the Confusion Assessment Method for the Intensive Care Unit (CAM-ICU) which is performed in two steps [43, 44]. First, level of arousal/agitation will be assessed with the Richmond Agitation Sedation Scale (RASS) [45, 46]. This is a 10-point scale with four levels of anxiety or agitation (+1 restless to +4 combative), one level of alert and calm (0), and five levels of sedation or coma (−1 lethargy to −5 nonarousable). Second, delirium is diagnosed by the CAM-ICU. It detects four features of delirium: (a) acute onset of mental status changes or a fluctuating course, (b) inattention, (c) disorganized thinking, and (d) altered level of consciousness. Delirium is defined as a RASS score of −3 or higher, with features of both (a) and (b), accompanied by either (c) or (d). Coma is defined as a RASS score of −4 or −5 where CAM-ICU cannot be assessed.

Delirium episodes are classified into three motoric subtypes. Hyperactive delirium means that the RASS scores are persistently positive (+1 to +4) during every CAM-ICU positive assessment; hypoactive delirium means that the RASS scores are persistently neutral or negative (between 0 and −3) during every CAM-ICU positive assessment; and mixed delirium means that some RASS scores are positive (+1 to +4) whereas some RASS scores are neutral or negative (between 0 and −3) during every CAM-ICU positive assessment [47, 48].

### Patient recruitment and baseline data collection

The day before surgery (or Friday for those who will undergo surgery on next Monday), investigators who are authorized by the principal investigator will check the list of patients planned for surgery and their medical charts to identify potential participants according to our inclusion and exclusion criteria. They will then visit these patients to formally invite them for participation.

For patients who meet the inclusion/exclusion criteria and give written informed consents, baseline data including demographic data, preoperative diagnosis, medical history, medication history, surgical history, and main results of physical, laboratory, and instrumental examinations will be collected. The following preoperative evaluation will also be performed, i.e., the activities of daily living are assessed with Barthel Index [49, 50], cognitive function is assessed with the Mini-Mental State Examination [51, 52], levels of anxiety and depression are assessed with the Hospital Anxiety and Depression Scale [53, 54], delirium is assessed with the CAM-ICU [43, 44].

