### Randomization

The randomization will be performed centrally at Peking University Clinical Research Institute through an interactive web response system (IWRS, Brightech Clinical Information Management System) on the day of surgery just before anesthesia. The randomization is stratified by medical center and type of surgery (thoracic or abdominal surgery) (Fig. 1).

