#### Primary outcome

The primary outcome is the 7-day incidence of postoperative delirium. Patients will be assessed for delirium with the CAM-ICU twice daily (from 8 to 10 a.m. and from 6 to 8 p.m.) during the first seven days after surgery. Study personnel who assess delirium do not participate in intraoperative anesthesia and postoperative management of patients.

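### Delirium is screened for before surgery, but a positive result is not a named exclusion and the primary outcome does not require new onset

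*Protocol article*

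**What the plan says.** All references are to the protocol article.

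- **Patient recruitment and baseline data collection.** The preoperative evaluation is introduced with the words "For patients who meet the inclusion/exclusion criteria and give written informed consents, baseline data". Among its items, "delirium is assessed with the CAM-ICU". No action is attached to a positive result.
- **Participants.** Preoperative delirium is not named among the exclusions. The closest criterion covers patients "unable to complete preoperative assessment due to severe dementia, language barrier or end-stage disease". The last criterion is open-ended: "any other conditions that were considered unsuitable for study participation".
- **Ethics approval.** Consent may come from someone else: "if the patient cannot provide informed consent, from the surrogate of the patient".
- **Randomization.** Allocation takes place "on the day of surgery just before anesthesia", so the screening result is known by then.
- **Personnel training and delirium assessment.** A case is a RASS score of −3 or higher with the required combination of CAM-ICU features. The acute-onset or fluctuation feature is not tied to the time of surgery, and no negative baseline is required.
- **Primary outcome.** "The primary outcome is the 7-day incidence of postoperative delirium". "Patients will be assessed for delirium with the CAM-ICU twice daily" over the first seven days.
- **Data analysis.** The analysis is by intention to treat and includes all subjects. Time to onset of delirium is one of the planned time-to-event results.

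**The concern.** An incidence presupposes people who are free of the event at the start. The trial makes the measurement that would establish this, at the right time, but neither the stated eligibility criteria nor the stated outcome definition uses it. A patient who is delirious but can complete the assessment falls under none of the three reasons in the nearest exclusion, and lack of capacity does not bar entry because surrogate consent is allowed.

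If such a patient is randomised and is still CAM-ICU positive after surgery, the case definition is met, although the anaesthetic technique could not have prevented that delirium. These events would add the same non-preventable amount to both arms, pull the relative risk toward 1 and cost power. Time to onset is also undefined for a patient who is already delirious.

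**Working it through.** **Inputs from Sample size estimation:** general-anaesthesia rate p₁ = 0.131; 30% relative reduction, so p₂ = 0.7 × 0.131 = 0.0917; two-sided α = 0.05; stated power 90%; 832 per group before dropout.

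**Assumed input:** f, the share positive before surgery who all remain positive afterwards. The protocol gives no figure; f = 0.5%, 1% and 2% are used.

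**Step 1. The plan's own figure.** For two proportions with pooled variance under the null and p̄ = (p₁ + p₂)/2:

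n = [1.96 √(2p̄(1−p̄)) + 1.2816 √(p₁(1−p₁) + p₂(1−p₂))]² / (p₁−p₂)²

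With p̄ = 0.11135 this is (0.8719 + 0.5690)² / 0.0393² ≈ 1,345 per group, not 832. Power at 832 per group is

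Φ{[0.0393 × √832 − 0.8719] / 0.4440} = Φ(0.589) = 72.2%.

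The stated sample size therefore does not reproduce. That is a separate problem in the sample size section, and 72.2% serves here only as the starting value.

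**Step 2. Add the prevalent cases.** The observed rate in each arm becomes p′ = f + (1−f)p. The relative risk is p₂′/p₁′. The risk difference is (1−f)(p₁−p₂), because the added cases cancel and only the factor (1−f) remains. Example for f = 1%: p₁′ = 0.01 + 0.99 × 0.131 = 0.1397; p₂′ = 0.01 + 0.99 × 0.0917 = 0.1008; relative risk 0.72; difference 0.99 × 3.93 = 3.89 points.

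| Assumed f | Rate, GA | Rate, EGA | Relative risk | Difference (points) | Power, 832 per group | Loss (points) |
|---|---|---|---|---|---|---|
| 0 | 13.10% | 9.17% | 0.70 | 3.93 | 72.2% | – |
| 0.5% | 13.53% | 9.62% | 0.71 | 3.91 | 70.3% | 1.9 |
| 1% | 13.97% | 10.08% | 0.72 | 3.89 | 68.5% | 3.7 |
| 2% | 14.84% | 10.99% | 0.74 | 3.85 | 64.9% | 7.3 |

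Most of the power loss comes from the higher event rates, which raise the variance; the difference itself hardly moves.

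**Step 3. Leave these patients out instead.** With n(1−f) per group and the original rates, power at 832 per group is 72.0%, 71.8% and 71.4% for the three values of f. Restricting the analysis recovers nearly all of the loss.

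**Step 4. Patients affected.** Of 1,800 enrolled, the three values of f correspond to 9, 18 and 36 patients.

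The calculations ignore the planned stratification by center and type of surgery.

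**The case against.** A reader might infer that the protocol counts pre-existing delirium as a postoperative event. It does not say so. It is silent on patients positive at baseline, and an incidence of postoperative delirium can be read in the ordinary sense of new cases after surgery. What the text supports is narrower: the stated definitions do not rule such a case out.

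The number of such patients may well be very small. Candidates come from the list of planned operations, must agree to patient-controlled analgesia, and are excluded for severe sepsis or if severe dementia or end-stage disease prevents assessment. The open-ended last exclusion lets an investigator turn a delirious patient away. These points narrow the gap. They do not close it, because that criterion is discretionary and could be applied differently across the five centers.

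The effect measure also matters. For the primary outcome the plan names a confidence interval for the difference between groups and no relative risk, and that difference barely changes. This stands.

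Finally, the handling of baseline-positive patients in the analysis could sit in a full protocol or analysis plan that is not shown. That is a fair reply on the denominator. It is weaker on eligibility, which the article sets out in detail, down to laboratory cut-offs, and which an analysis plan cannot change once patients have been enrolled.

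**Conclusion.** The point holds as a cheap improvement. Preoperative delirium is measured before randomisation, is not a named exclusion, and is not ruled out by the case definition or the primary outcome. A patient delirious before and after surgery could therefore be enrolled and meet the outcome.

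The size is modest and conditional. It rests on an assumed prevalence of 0.5% to 2% and on every such patient staying positive, which is the least favourable case. On that basis the cost is about 2 to 7 points of power and a slight attenuation of the relative risk.

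Two stronger readings are not supported. Because the screen precedes randomisation, these cases should balance, so there is no reason to expect bias toward either arm. And the gap between the stated 90% power and 72% does not come from this issue; it is already present at f = 0.

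**What to change.** 1. Add a positive preoperative CAM-ICU to the exclusion criteria, applied before randomisation.
2. State that the primary outcome is new-onset delirium within seven days after surgery.
3. For patients already enrolled, restrict the primary-outcome analysis to those CAM-ICU negative at baseline, and report the full intention-to-treat set as a sensitivity analysis. Because the restriction uses a result recorded before allocation, it preserves the randomised comparison. It should be fixed without reference to outcomes by arm.

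The cost is a protocol amendment with IRB review, since recruitment is under way and the Ethics approval section requires review of any modification. Eligibility changes mid-trial, and probably a few patients are lost. The third item also narrows the stated rule that all subjects are analysed, so it must be pre-specified and described openly as a restriction of the intention-to-treat set. No new data collection is needed.

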### Randomization

The randomization will be performed centrally at Peking University Clinical Research Institute through an interactive web response system (IWRS, Brightech Clinical Information Management System) on the day of surgery just before anesthesia. The randomization is stratified by medical center and type of surgery (thoracic or abdominal surgery) (Fig. 1).

**Fig. 1 Fig1:**
[figure not shown]
Design of the study

### Anesthesia and postoperative analgesia

For patients of both groups, no premedication is administered; dexmedetomidine is not allowed; anticholinergics are prohibited unless being used for the treatment of bradycardia, in which case atropine will be administered. Intraoperative monitoring includes electrocardiogram, non-invasive blood pressure, pulse oxygen saturation, end-tidal concentrations of inhalational anesthetics and carbon dioxide, nasopharyngeal temperature, and urine output. Radial arterial pressure and central venous pressure are monitored when necessary.

#### General Anesthesia plus Postoperative Intravenous Analgesia (GA Group)

For patients assigned to receive general anesthesia plus postoperative intravenous analgesia (GA Group), anesthesia will be induced with midazolam (0.02-0.03 mg/kg), propofol, sufentanil and rocuronium. For patients with expected difficult airway, endotracheal intubation may be facilitated by succinylcholine or awake intubation may be performed. Anesthesia will be maintained with either intravenous (propofol), inhalational (sevoflurane with or without nitrous oxide), or combined intravenous-inhalational anesthetics. Additional opioids (remifentanil, sufentanil, fentanyl, or morphine) and muscle relaxant (rocuronium, atracurium, or cisatracurium) will be administered when deemed necessary by the attending anesthesiologists.

Patient-controlled intravenous analgesia will be provided after surgery. This is established with 50 mg morphine in 100 mL normal saline, programmed to deliver a 2-mL bolus with a 6–10 minutes lockout interval and a 1 mL/hr background infusion. For patients with low body weight or poor general condition, doses can be decreased and upper dose limit can be set for the patient-controlled pump.

#### Combined Epidural-General Anesthesia plus Postoperative Epidural Analgesia (EGA Group)

For patients assigned to receive combined epidural-general anesthesia plus postoperative epidural analgesia (EGA Group), epidural catheterization will be performed first. The intervertebral space for epidural puncture will be selected by the attending anesthesiologists according to the site of planned incision. An epidural catheter will be inserted using a standard technique. After negative aspiration for blood and cerebrospinal fluid, a test dose of 3–4 mL of 2 % lidocaine will be administered to confirm the position of the catheter.

General anesthesia will also be induced with midazolam (0.02-0.03 mg/kg), propofol, sufentanil and rocuronium. Anesthesia will be maintained with intravenous (propofol), inhalational (sevoflurane with or without nitrous oxide), or combined intravenous-inhalational anesthetics, together with 0.375 %–0.5 % ropivacaine administered bolusly and/or continuously through the epidural catheter. Additional opioids (remifentanil, sufentanil, fentanyl, or morphine) and muscle relaxant (rocuronium, atracurium, or cisatracurium) will be administered when deemed necessary.

Patient-controlled epidural analgesia will be provided after surgery. This is established with 0.12 % ropivacaine and 0.5 μg/mL sufentanil in 250 mL normal saline, programmed to deliver a 2-mL bolus with a lockout interval of 20 minutes and a background infusion of 4 mL/hr. For patients with low body weight or poor general condition, doses can be decreased and upper dose limit can be set for the patient-controlled pump.

All anesthesiologists participating in the study will be experienced in epidural block techniques. But even in experienced hands, we can anticipate a failure rate of about 5 %. Patients with unsuccessful epidural blocks will receive general anesthesia and postoperative intravenous analgesia as that for the GA Group. However, data of these patients will be included in the EGA Group in the final intention-to-treat analysis (Fig. 1).

